### **8.6.3. Change of Treatment**

For many reasons patients operations are cancelled, or patients withdraw themselves from the surgical waiting list. If patients have been randomised into the study and then do not go on to have surgery; reasons for cancellation/withdrawal will be recorded, if available and patients, if willing, will be followed up accordingly.

In the event of discontinuation or withdrawal from the trial the reason will be recorded on the Case Report Form (CRF). Analysis will be performed on an intention-to-treat basis.

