### 709 **11.4. Procedure for Accounting for Missing, Unused, and Spurious Data**

710 Missing data will be minimized. Missing data will be reported and summarized by treatment arm. The  
711 distribution of missing data will be explored to assess the assumption that data are missing at random  
712 and multiple imputation will be utilized as appropriate with sensitivity analyses undertaken to explore  
713 the missing assumptions.

714 A more detailed account of analysis will be available in the statistical analysis plan and the health  
715 economic analysis plan.

716 Intention-to-treat analysis will be used with all patients will analysed in the group they were randomised  
717 to, regardless of treatment actually received. Sensitivity analyses will be carried out on a per-protocol  
718 population, to be fully defined in the statistical analysis plan.

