#### 3.2 Randomisation and Blinding

Randomisation between intervention and control will be 1:1, and will be stratified by study centre and operation type (Total Knee Replacement (TKR) or Unicompartmental Knee Replacement (UKR)). Randomisation will be performed using the RRAMP internet system provided by the Oxford Clinical Trials Research Unit (OCTRU). Where possible, randomisation will occur in theatre at the time of surgery either by a member of the clinical research team or a member of the surgical team. If not possible, randomisation can occur on days prior to the surgery to allow for time to coordinate the drug supplies and inform the operative and anaesthetic team. If consent has occurred more than a day before randomisation, the local research team will verbally check the patient still agrees to participation before proceeding with randomisation.

Full details of the randomisation are available in SPAARK\_RBP\_v3.0\_19Apr2018, stored in the confidential statistical section of the TMF.

The patient will be blinded to the treatment allocation. Unblinding will be performed on an individual basis as clinical need dictates. Surgeons who administer the medication cannot be blinded to treatment allocation; however, blinding of surgeons and outcome assessors is not necessary as the two co-primary outcomes are patient reported measures.

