### 4.2 Definition of Analysis Populations

Populations for analysis are defined as follows:

Intention to treat (ITT): all participants randomised in their randomised groups.

Per protocol (PP): participants who received the allocated intervention will be analysed according to the treatment they actually received. Participants will be excluded from the PP population if:

- They did not receive the treatment to which they were randomised
- They did not provide sufficient follow-up data for analysis
- They did not satisfy the eligibility criteria for the study

The definition of the PP analysis population will be finalised during a blinded analysis of the data (not separated by treatment group) prior to the final data lock.

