## 5.5 Description of Compliance with Intervention

The trial and control drugs are administered as a single intra-operative dose via peri-articular infiltration. Amount of drug administered will be recorded. As such patient compliance is not relevant to these drugs. If, for any reason, the randomised intervention is not delivered, this will be recorded along with the reason for not receiving the randomised treatment. The instances will be summarised by treatment group as outlined in Table 6. Any differences between the two treatment groups will be explored. In addition, the number of participants experiencing complications during surgery and the total number of complications during surgery will be summarised by treatment group (Table 7), and any differences will be investigated. The types of complications as well as their Clavien-Dindo classification will be summarised.

Summaries will also be provided on time from randomisation to surgery, time in theatre, type of surgery performed and whether this matched the type of surgery planned at randomisation, number of anaesthetists, surgeons and nursing staff present and their grades, ASA grade and anaesthetic used (see Table 7).

**Table 6:** Details of interventions received split by randomised treatment group

|                                                         | Intervention |   | Control |    |
|---------------------------------------------------------|--------------|---|---------|----|
|                                                         | n            | % | n       | %  |
| Received allocated intervention as planned a | X            | X | X       | X  |
| Didn't receive allocated intervention as planned        | X            | X | X       | X  |
| Did not have surgery                                    | X            | X | X       | X  |
| Reason(s) (repeat as needed)                            | X            | X | X       | X  |
| Received alternate trial treatment                      | X            | X | X       | X  |
| Reason(s) (repeat as needed)                            | X            | X | X       | X  |
| Received a non-trial treatment b             | X            | X | X       | X  |
| Reasons(s) (repeat as need)                             | X            | X | X       | X  |
| Did not receive all syringes as planned c    | X            | X | NA      | NA |

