#### 6.7 Harms

A serious adverse event (SAE) is any untoward medical occurrence that results in death, is life-threatening, requires inpatient hospitalisation or prolongation of existing hospitalisation, results in persistent or significant disability/incapacity, consists of a congenital anomaly or birth defect or is otherwise considered medically significant by the investigator.

Any adverse event (AE) occurring within 30 days of surgery will be recorded if there is a reasonable possibility it is related to either: (i) the administration of the investigational medical product (IMP) or the

control drug; or (ii) the knee replacement surgery. Expectedness and causality of AEs and SAEs will also be determined. AEs occurring more than 30 days following surgery will only be recorded if (i) the event is deemed to be serious (meets SAE criteria) and there is a reasonable possibility it is related to the knee replacement surgery; or (ii) there is a patient death.

Details of expected events related to either the administration of the IMP during surgery or the knee replacement surgery itself are provided in the trial protocol. It is noted that reported AEs related to the IMP have been shown to occur at a similar rate as those in the corresponding bupivacaine hydrochloride controls in active comparator studies.

The number of AEs occurring up to 30 days post-surgery will be reported by treatment group. The number of participants experiencing an AE will also be reported by treatment group, and the two groups will be compared. The number of SAEs, SARs, and SUSARs occurring up to 12 months post-randomisation will be reported by treatment group (Table 15). The numbers of participants experiencing an SAE, SAR or SUSAR will also be summarised by treatment group and will be compared between the liposomal bupivacaine + bupivacaine hydrochloride and bupivacaine hydrochloride alone groups by examination of the 95% confidence intervals for the difference in incidence. The analysis will be conducted for the ITT population as defined in Section 7. The number of deaths per arm will also be compared. Descriptive data on the type of AE reported, as well as MedDRA codes for the SAEs will also be presented.

**Table 15:** Summary of Serious Adverse Events (SAEs) including SARs/SUSARs

|                                                                        | Intervention | Control | Total |

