## 6.8 Health Economics and Cost Effectiveness (where applicable)

Health Economic Analysis: A cost utility analysis will also be performed using quality-adjusted life years (QALYs) as the main health outcome, obtained using the EuroQol EQ5D-5L questionnaire at baseline, 72 hours, 6 weeks, 6 months and 1 year. The perspective of the analysis will be societal and costs will be informed by collecting data on the initial surgery, cost of treatment and analgesic medication, primary/hospital and social care resource use over the first year following surgery, out-of-pocket expenses (e.g. over the counter medications, travel costs to attend consultations, private practitioners, etc.), unpaid care from family members or friends and loss of earnings resulting from knee replacement. Such data will be collected from hospital medical records and using self-completed patient questionnaires at 6 weeks, 6 months and 12 months. Healthcare and social care utilisation will be valued using national databases [25, 26].

The results of the cost utility analysis will be presented using an incremental cost-effectiveness ratio expressed as cost per QALY gained and interpreted as the additional costs/savings associated to the additional QALY benefits of Liposomal bupivacaine compared to bupivacaine hydrochloride.

The statistician is not undertaking this analysis. A separate Health Economic Analysis Plan (HEAP) will be drafted by the trial health economist.

636

637 **6.9 Meta-analyses (if applicable)**

638 There is no planned meta-analysis in this study.

639

640 **7. VALIDATION OF THE PRIMARY ANALYSIS**

641 To validate the co-primary outcomes a statistician not involved in the trial will independently repeat the  
642 analyses detailed in this SAP, by using different statistical software (if possible). The results will be compared  
643 and any discrepancies will be reported in the Statistical report (See OCTRU SOP STATS-005 Statistical  
644 Report).

645

646 **8. SPECIFICATION OF STATISTICAL PACKAGES**

647 All analysis will be carried out using appropriate validated statistical software such as STATA, SAS, SPLUS or  
648 R. The relevant package and version number will be recorded in the Statistical report.

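### Harms are compared only as randomised; adding a table by product received would remove a probably small dilution and keep rare drug reactions in the right column

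*Combined protocol and SAP*

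**What the plan says.** SAP 6.7 (Harms) sets the population in one sentence: "The analysis will be conducted for the ITT population as defined in Section 7". SAP Section 7 is headed "7. VALIDATION OF THE PRIMARY ANALYSIS" and defines no population. The only definition in the SAP is in 4.2: "Intention to treat (ITT): all participants randomised in their randomised groups". Protocol 11.4 agrees: "all patients will analysed in the group they were randomised" to, whatever they received.

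SAP 4.2 defines one other population, per protocol. SAP 6.4 uses it for the co-primary outcomes only. It could not serve for harms in any case, because it drops patients who did not receive their allocated treatment and does not regroup them. SAP 6.6 plans nothing further.

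The documents allow for patients whose exposure differs from their allocation:

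- Protocol 8.6.3 covers cancellations: "If patients have been randomised into the study and then do not go on to have surgery", reasons are recorded and willing patients are followed up.
- SAP 5.5, Table 6, has rows for no surgery, for a non-trial treatment and for "Received alternate trial treatment".
- SAP 3.2 prefers randomisation in theatre, but where that is not possible "randomisation can occur on days prior to the surgery to allow for time to coordinate the drug supplies".

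Protocol 10.1 defines adverse events and reactions by the product that was administered. Protocol 10.3 and SAP 6.7 record AEs within 30 days of surgery if they may be related to the drug or the operation. SAP 6.7 compares the arms through 95% confidence intervals for the difference in incidence.

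**The concern.** The event definitions depend on exposure and the comparison depends on allocation. The two part company for two kinds of patient.

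- **Not operated on.** With no surgery there is no 30-day window and no trial drug. The patient cannot have a recordable related AE but still counts in the denominator.
- **Given the other trial drug.** Any reaction is tabulated under the allocated arm, that is, under a product the patient did not receive.

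Both pull the difference in incidence towards zero. For a product that the protocol describes as unlicensed in the UK, that is the less cautious direction for a harms comparison. For SARs and SUSARs, where counts are likely to be very low, the position of a single event can change how the table reads.

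**Working it through.** **Arm size.** The plan gives no figure for the harms comparison, so the only stated figure to reproduce is the sample size in SAP 3.3. For QoR-40, with a 5-point difference, SD 15.5, two-sided 0.025 and 90% power:

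n = 2 × (2.2414 + 1.2816)² × (15.5/5)² = 2 × 12.41 × 9.61 ≈ 239 per arm (240 stated), and 240/0.96 = 250.

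The 250 per arm is used below.

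**Model.** Let u be the share of each arm not operated on (taken as equal in both arms, with no related AE possible). Let c_T and c_C be the shares of the intervention and control arms given the other trial drug, and p_T and p_C the related-AE risks by product received. Then:

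- Intervention arm, ITT: (1 − u − c_T) p_T + c_T p_C
- Control arm, ITT: (1 − u − c_C) p_C + c_C p_T
- Difference, ITT: (1 − u − c_T − c_C)(p_T − p_C)

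**Inputs.** The documents give no values for u, c_T, c_C or the AE risks. All of them are assumptions here. Power is for 250 per arm at two-sided 0.05.

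| u, c_T, c_C | Share kept | 20% v 10%: difference (power) | 10% v 5%: difference (power) |
|---|---|---|---|
| 0, 0, 0 | 100% | 10.0 points (88.2%) | 5.0 points (56.5%) |
| 1%, 1%, 0 | 98% | 9.8 (87.2%) | 4.9 (55.3%) |
| 2%, 2%, 2% | 94% | 9.4 (84.5%) | 4.7 (52.1%) |
| 5%, 5%, 5% | 85% | 8.5 (77.8%) | 4.25 (45.5%) |
| 10%, 5%, 5% | 80% | 8.0 (74.6%) | 4.0 (42.9%) |

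For the third row at 20% v 10%: intervention 0.96 × 20% + 0.02 × 10% = 19.4%; control 0.96 × 10% + 0.02 × 20% = 10.0%; difference 9.4 points.

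**Scale against sampling error.** At 20% v 10% with 250 per arm, the 95% half-width is 1.96 × √((0.16 + 0.09)/250) ≈ 6.2 points. A shift of 0.2 to 0.6 points is at most a tenth of that.

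**Rare events.** One event is 1/250 = 0.4 points. If one SAR is counted in the wrong arm, the difference moves by 0.8 points, and a true split of 1 v 0 appears as 0 v 1.

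**Limits of the model.** It describes related AEs. SAEs from any cause can occur in unoperated patients, so the formula does not carry over to them unchanged. Unoperated patients who are equally common in both arms shrink the risk difference but leave the risk ratio for surgery-linked events as it is; crossover shrinks both. The SAP uses the difference.

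**The case against.** The strongest case for leaving the plan alone has four parts.

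**ITT is defensible for harms.** SAEs and deaths are counted to 12 months from randomisation, for which an all-randomised comparison is coherent. Surgeons are not blinded, so who gets the other drug, or none, may depend on patient risk. Regrouping by product received gives up the protection of randomisation and can bias in either direction. This stands, and it is why ITT should not be demoted for 12-month SAEs and deaths.

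**Deviations should be few.** There is a single intra-operative dose, and randomisation is meant to be close to surgery. Table 6 is an empty shell that lists possible deviations and predicts no rate. This stands as to size. It does not remove unoperated patients, because earlier randomisation is allowed.

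**The assumed AE contrast is generous.** Both documents say that AE rates resemble those of bupivacaine hydrochloride controls. Both arms receive 100 mg of that drug, and surgical AEs are counted too. Crossover can dilute only the risk that comes from the liposomal component. This also stands: the risks in the table are illustrations.

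**Individual safety review is untouched.** A reader might infer that SUSAR reporting or DSMC oversight is compromised. The documents do not support that. Causality and expectedness are judged event by event (protocol 10.2 to 10.5), and the DSMC reviews related SAEs. The ITT grouping affects the end-of-trial comparison, and Table 6 would show how many patients crossed over.

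A reader might also infer from the reference to Section 7 that the harms population is undefined. It is not: 4.2 holds the only ITT definition, and the analysis methods in SAP 6.2 cite it correctly. The pointer is a slip.

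None of these points supplies a harms comparison by product received.

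**Conclusion.** The point holds as a gap beside the ITT table. An ITT harms table is not invalid in itself. What is missing is any tabulation of harms by what patients received, although the protocol defines reactions by the product given and the plan allows for unoperated and crossed-over patients.

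The direction is towards no difference under the simple model above, which assumes equal unoperated shares in the two arms. The size is unknown because the documents give no deviation rates. With assumed deviations of 1 to 2% per type, about 94 to 98% of the difference is kept, which is small beside sampling error. Losses of 15 to 20% need 5% crossover each way together with 5 to 10% unoperated, and nothing in the documents points to rates that high. A reader might infer that a material excess of common AEs would be hidden; the documents do not support that. The more tangible risk is one rare SAR or SUSAR standing in the wrong column.

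This is a cheap improvement.

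**What to change.** - In SAP 4.2, add a safety population: all randomised patients who received any trial injection, grouped by the product actually received.
- In SAP 6.7, report AEs, SARs and SUSARs, and also SAEs, in that population beside the ITT version of Table 15.
- Keep the ITT comparison for SAEs and deaths to 12 months.
- Correct the cross-reference in 6.7 from Section 7 to Section 4.2.

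No new data are needed. The amount of drug given and the reasons for non-delivery are already recorded (protocol 9.4, SAP 5.5), and Tables 8 and 9 already select patients who received liposomal bupivacaine. The cost is some SAP wording and one extra table. The downside is that the grouping is not randomised for the few patients who deviated, so the new table should say so and be read together with Table 6.

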## 6.8 Health Economics and Cost Effectiveness (where applicable)

Health Economic Analysis: A cost utility analysis will also be performed using quality-adjusted life years (QALYs) as the main health outcome, obtained using the EuroQol EQ5D-5L questionnaire at baseline, 72 hours, 6 weeks, 6 months and 1 year. The perspective of the analysis will be societal and costs will be informed by collecting data on the initial surgery, cost of treatment and analgesic medication, primary/hospital and social care resource use over the first year following surgery, out-of-pocket expenses (e.g. over the counter medications, travel costs to attend consultations, private practitioners, etc.), unpaid care from family members or friends and loss of earnings resulting from knee replacement. Such data will be collected from hospital medical records and using self-completed patient questionnaires at 6 weeks, 6 months and 12 months. Healthcare and social care utilisation will be valued using national databases [25, 26].

The results of the cost utility analysis will be presented using an incremental cost-effectiveness ratio expressed as cost per QALY gained and interpreted as the additional costs/savings associated to the additional QALY benefits of Liposomal bupivacaine compared to bupivacaine hydrochloride.

The statistician is not undertaking this analysis. A separate Health Economic Analysis Plan (HEAP) will be drafted by the trial health economist.

636

637 **6.9 Meta-analyses (if applicable)**

638 There is no planned meta-analysis in this study.

639

640 **7. VALIDATION OF THE PRIMARY ANALYSIS**

641 To validate the co-primary outcomes a statistician not involved in the trial will independently repeat the  
642 analyses detailed in this SAP, by using different statistical software (if possible). The results will be compared  
643 and any discrepancies will be reported in the Statistical report (See OCTRU SOP STATS-005 Statistical  
644 Report).

645

646 **8. SPECIFICATION OF STATISTICAL PACKAGES**

647 All analysis will be carried out using appropriate validated statistical software such as STATA, SAS, SPLUS or  
648 R. The relevant package and version number will be recorded in the Statistical report.

| CI     | Chief Investigator                            |
| AE     | Adverse Event                                 |
| SAE    | Serious Adverse Event                         |
| SAR    | Serious Adverse Reaction                      |
| SUSAR  | Suspected Unexpected Serious Adverse Reaction |
| AR     | Adverse Reaction                              |
| RCT    | Randomised Controlled Trial                   |
| QoR-40 | Quality of Recovery 40 Score                  |
| VAS    | Visual Analogue Scale                         |
| OKS    | Oxford Knee Score                             |
| AKSS   | American Knee Society Score                   |
| TMF    | Trial Master File                             |
| TKR    | Total Knee Replacement                        |
| UKR    | Unilateral Knee Replacement                   |
| SD     | Standard Deviation                            |
| OCTRU  | Oxford Clinical Trials Research Unit          |
| SITU   | Surgical Interventional Trials Unite          |
| SOP    | Standard Operating Procedure                  |
| ITT    | Intention-to-treat                            |
| PP     | Per Protocol                                  |
| MAR    | Missing at random                             |
| MI     | Multiple Imputation                           |

705

706

707
